## **2.2.4.2. The mechanistic or tympanometry sub-study outcomes**

### **Primary outcomes**

#### ***The change in middle ear effusion (MEE) at various time points***

We will assess the change in the MEE at the following time points: baseline visit, visit-1 (day-3), visit-2 (day-7), visit-3 (day-30), and visit-4 (day-90). We will measure MEE using static acoustic admittance, defined as “the amount of energy absorbed by the tympanic membrane and middle ear, measured in mmho or mL” [38]. We will also measure the difference of this results between the intervention and control group.

### **Secondary outcomes**

#### ***Duration of MEE***

We will also assess the duration to the resolution of MEE using tympanometry.

### The correlation between ear pain and other symptoms with the changes in MEE at various time points

We will identify the correlation between ear pain and other symptoms (i.e. ear tugging, irritability, crying, lack of sleep, lack of appetite, less of playfulness, fever) with the changes in MEE at various time points.

## 2.2.5 Participant timeline

Table 1 illustrates the timeline for visits and follow-ups. We will measure the outcomes at various time points: (1) visit-1 after the 48-hour observation (day-3); (2) visit-2 (day-7); (3) visit-3 (day-30); and (4) visit-4 (day-90). Patients will visit the hospital at visit-1 and visit-2, whilst the last two visits will be a home-visit. However, children in the mechanistic sub-study have to visit the hospitals at those follow-up visits. To improve the compliance of the study, the research personnel will send a daily text-message reminder to all the parents in the study during treatment period to take the drug, complete the symptom diary, and visit the clinic after the 48-hour expectant observation and other time points. At visit-2, parents will return the symptom diary and any left-over drug.

**Table 1.** Follow-up timeline

| TIMEPOINT                                                   | STUDY PERIOD         |                 |                           |                |                |                |
|-------------------------------------------------------------|----------------------|-----------------|---------------------------|----------------|----------------|----------------|
|                                                             | Enrolment Allocation | Post-allocation |                           |                |                | Close-out      |
|                                                             | 0 (Day-0)            | t1 (Day-3)      | Intervention ends (Day-5) | t2* (Day-7)    | t3* (Day-30)   | t4* (Day-90)   |
| ENROLMENT:                                           |                      |                 |                           |                |                |                |
| Eligibility screen                                          | X                    |                 |                           |                |                |                |
| Informed consent                                            | X                    |                 |                           |                |                |                |
| Allocation                                                  | X                    |                 |                           |                |                |                |
| INTERVENTIONS:                                       |                      |                 |                           |                |                |                |
| [Intervention A] Prednisolone (5 days)                      |                      |                 |                           |                |                |                |
| [Intervention B] Control (5 days)                           |                      |                 |                           |                |                |                |
| ASSESSMENTS:                                         |                      |                 |                           |                |                |                |
| Baseline examination (weight, height, BP, body temperature) | X                    | X               |                           | X              | X*             | X*             |
| Severity of pain and duration using VAS                     | X                    | X               |                           | X              |                |                |
| Overall symptoms and its duration using AOM-SOS             | X                    | X               |                           | X              |                |                |
| Adherence to trial drug                                     | X                    | X               |                           | X              |                |                |
| Adverse effects                                             | X                    | X               |                           | X              |                |                |
| Otoscopic examination                                       | X                    | X               |                           | X              | X*             | X*             |
| Tympanometry examination                                    | X +       | X +  |                           | X + | X + | X + |
| Complication                                                | X                    | X               |                           | X              |                |                |
| Recurrence of AOM                                           |                      |                 |                           |                | X*             | X*             |

BP=blood pressure; VAS=visual analogue scale; AOM-SOS: acute otitis media-severity of symptoms scale

\*The follow-up will be carried out by home-visit and phone, but those in the mechanistic sub-study will have their follow-up visits to the clinics; \*These time-point assessments will be applied only for children in the mechanistic sub-study

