| Outcome(s)              | 
(1) Outcome Name: Recruitment rates
 Metric/method of measurement: Informed consent form and case report forms (CRFs)
 The timepoint(s) of interest: Baseline visit (visit-0)
 
(2) Outcome Name: The success of the study procedures
 Metric/method of measurement: CRFs (i.e. eligibility and randomisation form, outcomes form)
 The timepoint(s) of interest: Baseline visit (visit-0)
 
(3) Outcome Name: Ability to measure planned outcomes in main study
 Metric/method of measurement: CRFs (i.e. eligibility and randomisation form, outcomes form) and symptom diary (e.g. Visual Analogue Scale/VAS and Acute Otitis Media – Severity of Symptoms Scale/AOM-SOS), and feedback form
 The timepoint(s) of interest: Baseline visit, visit-1 (day-3 to -5), visit-2 (day-7 to -9), day3, visit-3 (day-3 to -40), and visit-4 (day-90 to -100)
 
(4) Outcome Name: Compliance to study and study drug
 Metric/method of measurement: CRF (i.e. outcomes form), the symptom diary, and number of left-over drug
 The timepoint(s) of interest: Visit-1 (day-3 to -5), visit-2 (day-7 to -9), day3, visit-3 (day-3 to -40), and visit-4 (day-90 to -100)
 
(5) Outcome Name: The verification of sample size calculation for main study
 Metric/method of measurement: CRFs (i.e. eligibility and randomisation form)
 The timepoint(s) of interest: Baseline visit (visit-0)
 |

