### ***Ability to measure planned outcomes in the main study***

We will assess the ability to measure planned outcomes in main study, which are: (1) the proportion of children with pain reduced by at least the minimum clinically important amount, at day-3 after randomisation. This will be assessed using a VAS recorded in the patient symptom diary; (2) the severity of pain and other AOM-relevant symptoms at various time points using VAS, AOM-SOS, and the symptom diary; (3) duration to AOM resolution; (4) adverse effects, defined using standard clinical trials criteria, recorded in the diary, and reported to the central office and ethics committee as required.; (5) complications of AOM (e.g. perforation of tympanic membrane(s), mastoiditis); and (6) AOM recurrence, defined as a new episode of AOM at one to three months after randomisation. We will report these narratively due to a limited sample size and insufficient formal power calculation for this pilot study to be able to detect actual effects of corticosteroids to improve clinical outcomes in AOM.

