### 2.1.6 Sample size

We did not determine a sample size for the pilot study. There are several suggestions in calculating the sample size for a pilot study (e.g. at least 55 participants or at least 9% of the sample size of the main study) [39]. Since we will need 60 children in the mechanistic sub-study, we will include 60 children with AOM in our pilot study. The sample size of the mechanistic study was determined based on the main primary outcome, which is the mean value of static acoustic admittance or acoustic compliance in the tympanogram. In a previous study of children with middle ear effusion (MEE) who underwent tympanometry assessment and had a history of chronic or recurrent middle ear disease [40], the response within each subject group was normally distributed with standard deviation 0.3. If the true difference in the experimental and control means is 0.3 units, we will need to study 22 experimental subjects and 22 control subjects to be able to reject the null hypothesis that the population means of the experimental and control groups are equal with probability (power) 0.9. The Type I error probability associated with this test of this null hypothesis is 0.05. With a 20% allowance for dropouts, the total sample size becomes 56 or we will include 60 children for this pilot study.

Using the worst-scenario that of 50 physicians who work at seven appointed hospitals and have approximately 97 patients with AOM per week, we estimate that only 30% of the physicians will confirm their participation and 25% of the patients will give their consents to participate in our study. We then estimate that it will require nine months to recruit 60 children with AOM in this pilot study, including the extra months for potential slow recruitment and last follow-up (three months after the baseline visit).

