### **2.5.2 Harms**

An adverse event is defined as any untoward medical occurrence in a patient or clinical investigation subject administered a pharmaceutical product and which does not necessarily have to have a causal relationship with trial drug; whereas adverse effects or adverse drug reaction, is defined as all noxious and unintended responses to a trial drug related to any dose.

At the Visit-2 (Day-3), the appointed nurse is the first person who will identify any adverse effects (AEs). These will be identified by history taking (e.g. interview) and the symptom diary. The parents will provide information in the symptom diary regarding the adverse effects and whether they seek any treatment or medical assistance to manage AEs. The nurse then will report the adverse effects to the physicians along with the information of the intervention group which the child was allocated to. This information will be provided after the physician assess and record the primary outcome (i.e. ear pain three days after the randomization) on the 'Outcome form'. This is important to keep the concealment.

Adverse events and adverse drug reaction will be collected after they sign the written consents and being enrolled in the trial. All adverse events occurring after the enrolment into the study, during the additional treatment or hospitalization due to adverse events and/or ADR will be

recorded. A subject who experiences a serious adverse event (SAE), defined as any untoward medical occurrence at any dose that may result in-patient and/or prolonged hospitalization, persistent or significant disability, medically important events, life threatening events, and death, will receive sufficient treatment and will be recorded and reported to the Research Committee Ethics FMUI – CMH and the Bond University’s Human Research Ethics Committee (BUHREC). We will be responsible for any additional examinations and/or treatment that are required to manage AEs.

We will not report SAE occurring after the trial discontinuation, unless there is a temporal relationship between trial drugs or other protocol procedure to the events, as well as whether the event is unexpected or unexplained given the subject’s clinical course, previous medical conditions, and concomitant medications. All the SAE will be recorded in SAE form.

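### Table 1 schedules no adverse-effect or complication assessment after Day 7, and once the symptom diary ends at Day 14 no harms enquiry is specified for the last 76 of 90 days

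*Protocol*

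**What the plan says.** Table 1 in section 2.2.5 lists the assessments at each visit. The rows "Adverse effects" and "Complication" carry marks at Days 0, 3 and 7 and none at Days 30 and 90. In those two late columns the table does mark the general examination (weight, height, blood pressure, temperature), otoscopy, tympanometry and AOM recurrence.

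Section 2.5.2 (Harms) says that "All adverse events occurring after the enrolment into the study" will be recorded. It defines an adverse event without requiring a causal link to the drug, and an adverse effect as a response to the drug. The enquiry it describes is a nurse's interview at one early visit, together with the symptom diary.

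Section 2.2.3.3 has the third and last diary booklet cover Days 7 to 14. Section 2.4.1 likewise speaks of two weeks of diary completion.

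Section 2.2.4.1 counts adverse effects and "complications of AOM (e.g. perforation of tympanic membrane(s), mastoiditis" among the planned main-study outcomes whose measurability the pilot is to assess.

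On attendance at Days 30 and 90, section 2.2.5 provides home visits in general but adds: "However, children in the mechanistic sub-study have to visit the hospitals at those follow-up visits". The sample-size section states: "Since we will need 60 children in the mechanistic sub-study, we will include 60 children with AOM in our pilot study".

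**The concern.** Sites work from the schedule table. A site that follows Table 1 as written has no prompt to ask about adverse events or complications at Day 30 or Day 90, although the child is being seen. The general rule in section 2.5.2 then has no visit attached to it after the diary closes.

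Section 1.1.3 gives the main trial's follow-up of up to three months as one reason for running a pilot, and section 1.1.2 lists adverse effects and complications among that trial's secondary outcomes. If neither is asked about after the second week, the pilot cannot show whether they can be collected over the period the main trial will use. The only related evidence would come from the examinations and from serious-event reports.

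**Working it through.** The protocol states no figure for the share of follow-up covered by harms assessment, so there is none to reproduce. The check has three parts.

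**1. Length of the gap.** Inputs:
- last adverse-effect or complication mark: Day 7 (Table 1);
- end of the symptom diary: Day 14 (section 2.2.3.3);
- end of follow-up: Day 90 (Table 1), or up to Day 100 by the visit-4 window in the registration data set.

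Share of follow-up after the last planned harms capture = (end of follow-up − end of diary) / end of follow-up:
- Day 90 end: (90 − 14) / 90 = 76/90 = 84.4%;
- Day 100 end: (100 − 14) / 100 = 86/100 = 86.0%.

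This credits the diary with both adverse effects and complications up to Day 14. Section 2.5.2 says that the diary records adverse effects. The diary form itself (Appendix 5) is not shown, so the credit for complications is an assumption in the plan's favour.

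If both rows were marked at Days 30 and 90 and the question covered the interval since the last visit, no part of the 90 days would lie after the last scheduled enquiry.

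**2. What is still captured after Day 14.**

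| Type of event | Route after Day 14 | Scheduled? |
|---|---|---|
| Perforation still present at the visit | Otoscopy, Days 30 and 90 | Yes |
| Change in weight, blood pressure or temperature | General examination, Days 30 and 90 | Yes, though not labelled as harms |
| AOM recurrence | Own row in Table 1, Days 30 and 90 | Yes |
| Serious event, including hospital admission | Serious-event reporting, section 2.5.2 | Event-driven |
| Perforation that opened and healed between visits | None named | No |
| Complication treated and resolved without meeting the serious criteria | None named | No |
| Non-serious adverse event that resolved | General rule only, section 2.5.2 | No |

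The last three rows are the gap.

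**3. Whether the visits exist.** The mechanistic sub-study needs 60 children and the pilot enrols 60, so in effect every child is in the sub-study and attends hospital at Days 30 and 90. Recurrence is already asked about there. A harms question needs no new visit.

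One related label also needs reconciling. Section 2.5.2 calls the nurse's interview visit Visit-2 at Day 3, whereas section 2.2.5 makes Day 3 visit-1 and Day 7 visit-2.

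**The case against.** The strongest defence is that the Day 7 stop is deliberate and sensible. Prednisolone is given for five days and has a stated biological half-life of 12 to 36 hours. The diary therefore covers the whole course and nine further days (14 − 5). The Table 1 row concerns adverse effects, meaning reactions to the drug, so closing it soon after treatment is compatible with a standing rule to record all adverse events. Serious events are reportable, and section 2.6.7 adds a 24-hour emergency call and paid care for drug-related effects.

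Much of this stands. It shows that a share of calendar days does not measure missed harm, and the documents give no rate for late events. It does not answer the complication row: complications follow from the disease, are a named outcome, and do not end with the drug course. Nor does it give the rule in section 2.5.2 a visit at which it is carried out.

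Stronger readings are tempting, but the documents do not support them:
- From the Table 1 marks alone, a reader might infer that (90 − 7)/90 = 92% of follow-up lacks harms assessment. That ignores the diary.
- A reader might infer a flat contradiction with section 2.2.5, which says "We will measure the outcomes at various time points: (1) visit-1 after the 48-hour observation (day-3); (2) visit-2 (day-7); (3) visit-3 (day-30); and (4) visit-4" (Day 90), and with the registration data set, which lists visits 3 and 4 under "Ability to measure planned outcomes in main study". Both are pooled lists of visits for several outcomes. The pain scale and the symptom score are also blank at Days 30 and 90, so these lists cannot mean that every outcome is measured at every visit.
- A reader might expect late events to be lost unequally between arms because parents know the allocation. That is possible but speculative, and open-label knowledge would affect a late interview as well.
- Upper limits on event rates when none are seen depend on the number of children, not on the schedule. They add nothing here.

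**Conclusion.** The point holds as a minor one. Table 1 has no adverse-effect or complication mark after Day 7. From the end of the diary at Day 14, no scheduled enquiry about either is specified for 76 of 90 days (84%; 86% with a Day 100 end). This sits poorly with the promise in section 2.5.2 to record all adverse events after enrolment, and with the place of complications among the outcomes tested in section 2.2.4.1.

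The practical loss is mainly non-serious events and complications that arise and resolve between visits. How many there would be cannot be estimated from the protocol.

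The conclusion rests on two assumptions: that the diary captures harms through Day 14, and that the case report forms (Appendix 3, not shown) contain no late harms question that the protocol text omits. If the forms do contain one, only Table 1 needs to be brought into line.

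**What to change.** In Table 1, mark the complication row at t3 (Day 30) and t4 (Day 90). At the same two visits add an adverse-event enquiry, using that term as section 2.5.2 defines it. Word both as events since the last visit and ask them identically in both arms. In section 2.5.2, name these visits as the points at which adverse events are asked about after the diary ends, and correct the visit label for Day 3 there. If the Day 7 stop for drug reactions is intended, say so and keep the late enquiry for adverse events and complications.

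The cost is two rows of the table, a sentence or two in section 2.5.2, and a few interview items at visits that already take place. No visit, sample-size or treatment change is involved.

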## Participant enrolment

In the main study, we will stratify eligible children by the clinical specialty (primary care or secondary/tertiary care) and severity of AOM (mild or severe). However, we only include ear-nose-throat-specialists (ENTs) who work at tertiary care in this pilot study. Therefore, we will stratify the children based on their AOM severity and then will randomly allocate these eligible children to receive either a single dose prednisolone for five days or without, as an addition to expectant

observation in the mild AOM group or as an addition to antibiotics according to physicians' preferences (e.g. antibiotic type, dose, duration) in the severe AOM group (see Figure 1).

[figure not shown]

**Figure 1.** Flow chart of the stratification and randomization of the study

Participating physicians will assess the eligibility of children who come to the hospital based on their symptoms and clinical features of AOM. The eligible children will then be stratified based on the severity of AOM to either mild or severe AOM group. This process will be assisted using an eligibility and randomisation form. The participating clinicians will then obtain a clinical history and perform a baseline examination, including general, otoscopic, and tympanometry examination. The results of these procedures will be recorded at the baseline history form and outcomes form. The tympanometry examination will be conducted by an audiologist or a tympanometry technician. The physician will assess and analyse the tympanometry findings and record the results in the outcome form. After these procedures, the children will be sent to the appointed nurse who will perform the randomisation and dispense the prescription for a study medication (prednisolone) if the patient is assigned to the intervention group.

### 2.1.6 Sample size

We did not determine a sample size for the pilot study. There are several suggestions in calculating the sample size for a pilot study (e.g. at least 55 participants or at least 9% of the sample size of the main study) [39]. Since we will need 60 children in the mechanistic sub-study, we will include 60 children with AOM in our pilot study. The sample size of the mechanistic study was determined based on the main primary outcome, which is the mean value of static acoustic admittance or acoustic compliance in the tympanogram. In a previous study of children with middle ear effusion (MEE) who underwent tympanometry assessment and had a history of chronic or recurrent middle ear disease [40], the response within each subject group was normally distributed with standard deviation 0.3. If the true difference in the experimental and control means is 0.3 units, we will need to study 22 experimental subjects and 22 control subjects to be able to reject the null hypothesis that the population means of the experimental and control groups are equal with probability (power) 0.9. The Type I error probability associated with this test of this null hypothesis is 0.05. With a 20% allowance for dropouts, the total sample size becomes 56 or we will include 60 children for this pilot study.

Using the worst-scenario that of 50 physicians who work at seven appointed hospitals and have approximately 97 patients with AOM per week, we estimate that only 30% of the physicians will confirm their participation and 25% of the patients will give their consents to participate in our study. We then estimate that it will require nine months to recruit 60 children with AOM in this pilot study, including the extra months for potential slow recruitment and last follow-up (three months after the baseline visit).

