## CHAPTER 2 – METHODS

### 2.1 Trial design

This study is a pilot of a parallel, pragmatic, stratified, randomised, open-label, single-blind controlled trial of corticosteroids, as monotherapy for mild AOM, and in addition to individually prescribed antibiotics for severe AOM. In the main study, we will stratify eligible children based on the clinical specialty (primary care or secondary/tertiary care) and severity of AOM (mild or severe). However, for this pilot study, we only include ear-nose-throat-specialists (ENTs) who work at tertiary centres for the convenience of the implementation of the mechanistic sub-study as tympanometry is only available at the hospitals (tertiary centres). Therefore, we will stratify the children based on their AOM severity and then will randomly allocate to corticosteroid (prednisolone) or control (usual care without prednisolone) (Figure 1) with the allocation ratio of 1:1. Because it is an open-label study, the parents/caregivers and an appointed nurse who will perform the randomisation will be aware of treatment allocation, whilst the clinicians and tympanometry technicians will remain unaware of the treatment.

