#### **2.4.3 Statistical methods**

For the recruitment rate, we report the outcome as the proportion of children in percentages (%). For the success of the study procedures and the ability to measure planned outcomes in main study, we will report the outcomes as the proportion of clinicians in percentages based on the grading

scale of their feedback reporting on prespecified outcome measure tools. For the compliance to study and study drug, we will report the outcomes as the proportion of children in percentages who attend the follow-up visits and complete the cycle of study drug.

To assess the verification of sample size calculation for main study, we will report this outcome as the proportion of children in each stratum (mild and severe AOM group) and those with pain at Day-3 after randomisation in the control group.

For the mechanistic sub-study, we will report continuous variables (i.e. the change in MEE at various time points (mean in days standard deviation), the duration of MEE) as a mean difference (MD) with 95% confidence intervals (CI) also the difference between two groups. We also will report the correlation between ear pain and other symptoms with the changes in MEE at various time points.

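### The sub-study's 90% power is worked out for one comparison of mean admittance, but its primary outcome is change at four visits with none designated primary

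*Protocol*

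**What the plan says.** Section 2.1.6 bases the size of the mechanistic sub-study on "the main primary outcome, which is the mean value of static acoustic admittance or acoustic compliance in the tympanogram". From an earlier study it takes that "the response within each subject group was normally distributed with standard deviation 0.3". It continues: "If the true difference in the experimental and control means is 0.3 units", then "we will need to study 22 experimental subjects and 22 control subjects" to reject the hypothesis that "the population means of the experimental and control groups are equal with probability (power) 0.9". The type I error of 0.05 is attached to that one test. No visit is named. A 20% dropout allowance brings the total to 56, rounded to 60, and that number also fixes enrolment for the whole pilot.

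Section 2.2.4.2, under its heading for primary outcomes, describes a different quantity: "We will assess the change in the MEE at the following time points", followed by baseline and days 3, 7, 30 and 90. The measure is static acoustic admittance in mmho or mL, and the difference between the groups is to be assessed. No visit has priority.

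Section 2.4.3 repeats the multi-visit outcome, to be reported as mean differences with 95% confidence intervals, and describes it as "the change in MEE at various time points (mean in days standard deviation". Section 2.1 says that before randomisation "we will stratify the children based on their AOM severity".

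**The concern.** The sample size answers a question about one mean, while the declared primary outcome is a set of four changes. Two things follow.

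- **Power.** The SD of a change from baseline is not in general the SD of a single reading. It depends on how strongly baseline and follow-up correlate within a child, and the protocol does not give that correlation.
- **Error rate.** The 0.05 belongs to one test. With four co-equal visits the reader cannot tell which result the power and error statement supports, or whether one favourable visit would count as a positive finding.

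This matters beyond the sub-study. Section 1.2 gives it an efficacy aim, section 2.6.8.3 plans a separate paper for it, and its calculation sets the 60 children for the whole pilot. The instruction in section 2.2.4.1 to report narratively, for want of power, covers the planned main-study clinical outcomes and not tympanometry.

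**Working it through.** **Inputs from section 2.1.6:** difference 0.3, SD 0.3, alpha 0.05 (taken as two-sided; one-sided would give 18 per arm), power 0.9, dropout 20%. **Visits from section 2.2.4.2:** four after baseline. **Assumed, because the protocol gives no value:** ρ, the correlation between baseline and follow-up admittance, shown over a range; and equal variance at every visit.

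**1. The plan's own figure.** The standardised difference is 0.3/0.3 = 1. The normal approximation gives 2 × (1.960 + 1.282)² / 1² = 21.01, rounded up to 22 per arm. The exact two-sample t-test at 22 per arm has power 0.8997. For dropout, 22/0.8 = 27.5, so 28 per arm and 56 in total. The stated figures reproduce.

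**2. Power for a change score at one visit.** SD of change = 0.3 × √(2(1 − ρ)). Two-sample t-test, true difference 0.3, alpha 0.05:

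| ρ | SD of change | Power, 22 per arm | Power, 24 per arm |
|---|---|---|---|
| 0 | 0.424 | 0.63 | 0.67 |
| 0.3 | 0.355 | 0.78 | 0.82 |
| 0.5 | 0.300 | 0.90 | 0.92 |
| 0.6 | 0.268 | 0.95 | 0.97 |
| 0.7 | 0.232 | 0.99 | 0.99 |

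The 24 per arm is what remains of 60 enrolled after 20% loss (60 × 0.8 / 2). At 22 per arm the stated 90% is met at ρ = 0.5, missed below it and exceeded above it.

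**3. Overall error if any of four visits could count.** Four independent tests at 0.05 give 1 − 0.95⁴ = 18.5%. Changes that share a baseline are not independent. With equal variances σ² and equal correlations ρ between all visits, two changes have covariance σ²(1 − ρ) and each has variance 2σ²(1 − ρ), so they correlate at 0.5 whatever ρ is. Simulation from a multivariate normal at correlation 0.5 gives 15.6%. At 0.7 it is 13%, and at 0.8 it is 11.4%.

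**4. What a correction would cost.** With Bonferroni (0.05/4 = 0.0125) and SD 0.3, power is 0.76 at 22 per arm and 0.80 at 24. Keeping 90% would need 31 per arm by the t-test (30.17, rounded up).

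**5. One visit, adjusted for baseline.** The residual SD is 0.3 × √(1 − ρ²), which is never above 0.3. Power at 22 per arm for ρ = 0, 0.3, 0.5, 0.6 and 0.7 is 0.90, 0.92, 0.96, 0.98 and 0.995. The two degrees of freedom used by the covariates cost less than 0.001 (0.899 instead of 0.8997 at ρ = 0).

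**The case against.** Several stronger readings are tempting, and the protocol does not support them.

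- **That the sub-study is underpowered.** This would follow only if ρ were below 0.5. The protocol is silent on ρ, and above 0.5 the power exceeds 90%. The 90% is unproven for the declared outcome, not shown to be lost.
- **That the 5% error rate no longer applies.** It applies to each comparison. The 11% to 18.5% range presupposes that success at any one visit could be claimed, and no section states such a rule. Section 2.4.3 plans estimates with confidence intervals. Still, section 2.1.6 rests on a formal null-hypothesis test, and nothing says which visit that test belongs to.
- **That the planned analysis is unadjusted.** Section 2.4.3 says only mean difference with a confidence interval. An ANCOVA also yields that, and covariates may be set out in a statistical analysis plan that is not shown. The absence of the severity stratum from section 2.4.3 is therefore not a defect in itself, and no size can be put on it.
- **That the unit of days is a substantive error.** It sits in a garbled parenthesis next to the duration of effusion, and section 2.2.4.2 gives the right unit. It is an editorial slip.

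It could also be said that multiplicity belongs in the analysis plan. A multiplicity method may. But which outcome is primary, and whether the sample size was worked out for it, are matters for the protocol, and sections 2.1.6 and 2.2.4.2 disagree on them.

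**Conclusion.** The mismatch stands. The arithmetic in section 2.1.6 is correct for a single comparison of mean admittance, but the primary outcome in sections 2.2.4.2 and 2.4.3 is change at four visits with none designated primary. For that outcome the power per visit at 22 per arm lies anywhere from 0.63 to 0.99 for ρ between 0 and 0.7, and the protocol gives no basis for choosing within that range. If any visit could carry the claim, the overall error is about 16% under equal variances and equal correlations.

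All the power figures take the 0.3 SD at face value. It comes from children with chronic or recurrent middle ear disease, and whether it holds in acute otitis media cannot be checked from the protocol. Should-fix: the defect is real and leaves the headline result undefined, but wording cures it.

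**What to change.** Align sections 2.1.6, 2.2.4.2 and 2.4.3 on one primary comparison.

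1. Name one primary visit and say why. Day 7 is one reasoned option, being the first visit after the five-day course. Day 3 can also be argued, since it is the main study's primary time point. The choice is the investigators'.
2. Make the measure static admittance at that visit, analysed by ANCOVA, or by a mixed model over all visits, with baseline admittance and severity stratum as covariates. Both are already collected.
3. Make the other visits secondary.
4. In section 2.4.3 give the change in mmho or mL.

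Under the protocol's SD of 0.3, the statement of 22 per arm with 90% power then holds, to rounding, for any ρ. If the investigators prefer to keep four co-primary visits, they need a multiplicity rule, a justified SD of change and a new sample size.

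The recommended change needs no further children, visits or data. Its cost is the wording of three sections and the loss of primary status for the other visits.
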